### Objectives {7}

The primary objective of this randomized clinical trial is to analyse the effect of VR stimulation on the incidence of delirium after admission to the ICU. Participants in the control group will receive the standard ICU care, while participants in the intervention group will additionally receive VR stimulation. We hypothesize that participants receiving the VR stimulation will have a lower incidence of delirium during their stay in the ICU, compared to the control group. The secondary objectives are to evaluate differences in movement patterns and intensity between the intervention and control groups and between participants with delirium and without delirium. We expect that these differences will be related to the different types of delirium (i.e. hyperactive, hypoactive, or mixed). Additionally, it is predicted that it will be possible to detect differences in movement patterns between groups and identify patterns indicating the presence or absence of delirium. Secondary objectives also include the evaluation of the effect of VR on duration of delirium. In this case, it is hypothesized that the duration of delirium will be shorter in participants receiving the VR stimulation compared to those in the control group.

Further objectives which will be addressed include (1) evaluating the effect of VR stimulation, identified by changes in physiological parameters; (2) evaluating how easily the VR stimulation can be provided to patients by critical care professionals; (3) describing differences in cognition, health-related quality of life, and functional independence between groups, using questionnaires; and (4) evaluating if VR reduces the need for pharmacological treatment of delirium.

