Other pre-specified outcome variables include physiological parameters, feasibility of using the VR stimulation by ICU nurses, cognition at ICU discharge and 6 months post-discharge, health-related quality of life and functional independence before ICU admission and 6 months post-discharge, disease-related data, and survival 6 months post-discharge from the ICU. Physiological parameters (e.g. blood pressure, heart rate, respiration rate) will be recorded continuously and changes from baseline, or the start of an event such as VR stimulation, will be compared to later time points. The changes occurring in these parameters over time, together with disease-related data, are of interest and could indicate what effect, if any, VR stimulation has on the condition of the participant. Scores for health-related quality of life, functional independence, and clinical frailty before ICU admission and 6 months post-discharge, and cognition before ICU discharge and 6 months post-discharge, will be compared to determine if any significant differences occur. Additionally, the average survival 6 months post-ICU discharge will be compared between groups. Looking at these variables between groups is important as cognition, health-related quality of life, independence, frailty, and mortality, among others, are known to be negatively impacted by the presence of delirium during the time spent in the ICU. Therefore, it is meaningful to identify if there were any significant changes in these aspects for individuals in the treatment group compared to the controls. It will also be important to determine if providing such an intervention is feasible for the care providers. For this, the validated System Usability Scale will be completed by the nurses in order to understand if overall, the use of this technology was accepted and whether or not it could be integrated into standard ICU care practices [29].

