### Participant timeline {13}

Participant recruitment, enrolment, and allocation will all be targeted for the first 24 h following admission to the ICU. Once admitted, the participants will be monitored and evaluated, through a series of assessments, every day they are in the ICU up until their discharge, or at most, 14 days following ICU admission. A follow-up visit is planned for 6 months post-ICU discharge (Fig. 1).

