Movement and movement patterns will be recorded continuously at 100 Hz for the duration of the participants’ stay in the ICU, with AX3 Axivity (Axivity Ltd., Newcastle upon Tyne, UK) inertial measurement units attached to participant’s hands, legs, and chest and placed under the mattress (Sensing Tex, Barcelona, Spain). To enable accurate interpretation of this data, the participant’s environment will be recorded with a camera. This will allow for the distinction to be made between movements made by the participant and those from the interprofessional team or family members. To maximize the privacy of the participant, the camera will be mounted on the head-end of the bed, so the face of the participant is not visible.

Physiological parameters (e.g. non-invasive arterial blood pressure, heart rate, and respiratory rate) will be monitored by the in-house monitor system of the University Hospital (GE Healthcare, Little Chalfont, UK). Respiration and heart rate will be measured at a frequency of 240 Hz, while the blood pressure will be measured as the median every 2 min. A list of pharmacological agents provided to the participant and disease-related data will be collected via the patient data management system. While movement and physiological data will be recorded continuously throughout the patients’ stay in the ICU, the non-continuous assessments will also be completed at various time points (Fig. 1).

At the earliest opportunity, the participant—or, in the event of incapacity, his/her relatives—will be interviewed by the study team about their health-related quality of life, functionality, and frailty, using the EQ-5D instrument [38], the Functional Independence Measure [39, 40], and the Clinical Frailty Score [41], respectively, 1 week before ICU admission and 6 months post-discharge. The reliability and validity of the three-level EQ-5D, the EQ-5D-3L, is well established; however, the more recently expanded five-level version, the EQ-5D-5L, still lacks proper reliability and validity studies [38]. The Functional Independence Measure has a reliability score of *κ* > 0.85 [42, 43] and a high internal validity [42]. The Clinical Frailty Score has been found to have good reliability [44] and good construct validity [41].

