Cognitive impairment will be assessed by the study team before ICU discharge and 6 months post-discharge using the Montreal Cognitive Assessment [45]. The Montreal Cognitive Assessment has a known reliability of *κ* = 0.83 [45] and an established content validity in English and in French [45] and a sensitivity of at least 0.90 [46]. The average survival 6 months post-discharge will be obtained via a central database.

The study ends with a follow-up assessment 6 months after admission to the ICU. The study team interviews the participants during a regular follow-up session at the ICU. During the interview, the EQ-5D-5L, Functional Independence Measure, Clinical Frailty Score, and Montreal Cognitive Assessment will be administered. All assessments will be conducted according to the standard ICU care by trained ICU nurses.

In a final step following the VR intervention, the ICU nurse responsible for the intervention will be asked about the feasibility of applying the intervention, completing the 10-item System Usability Scale [29]. The System Usability Scale has a strong reliability score *κ* > 0.89 [47, 48] and an established construct validity, as well as concurrent validity (*r* = 0.86) [47, 48].

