### Methods in analysis to handle protocol non-adherence and any statistical methods to handle missing data {20c}

As suggested by the SPIRIT guidelines, we propose to test superiority using two analysis sets: the “intention-to-treat set”, considering all patients that are randomized regardless of whether they received the randomized treatment, and the “per protocol” set [49]. We propose declaring superiority of the experimental intervention only if shown superiority using both the “intention to treat” and the “per protocol” analysis set. As our study takes place in the ICU, it is expected that drop-outs will occur for medical reasons which make it unfeasible to continue in the study, but that are not related to the study itself. For this reason, there are two groups of participants who will be considered drop-outs. Firstly, any participant who can no longer continue in the study due to health reasons, before the first assessment for the primary outcome (i.e. the ICDSC) has been completed, will be considered a drop-out. Secondly, any participant for whom the neutral physician gave consent, but for whom the relatives withdrew consent, will be considered as a drop-out. Therefore, in order to maintain a sufficient sample size, it is important that these participants are replaced in a 1:1 manner, as approved by the local ethics committee. If a participant does drop-out of the study, their health status will be recorded at this point. As no long-term negative outcomes from the intervention are suspected, no further follow-up will be performed. If missing values occur within the dataset, we will use multiple imputation assuming missing data to be missing at random.

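### As worded, the between-arm comparison of change in cognition starts from a score taken after VR exposure, and the missing-at-random imputation rule makes no exception for death

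*Protocol article*

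**What the plan says.** Outcomes {12} lists the long-term scores among the other pre-specified outcome variables. It pairs two assessments for each. For three instruments the pair is "Scores for health-related quality of life, functional independence, and clinical frailty before ICU admission and 6 months post-discharge"; for cognition the sentence continues "and cognition before ICU discharge and 6 months post-discharge, will be compared to determine if any significant differences occur". A little further on, the section gives the purpose: "it is meaningful to identify if there were any significant changes in these aspects for individuals in the treatment group compared to the controls". Objectives {7} sets the matching aim as "describing differences in cognition, health-related quality of life, and functional independence between groups, using questionnaires".

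On timing, {18a} places the EQ-5D, Functional Independence Measure (FIM) and Clinical Frailty Score at "1 week before ICU admission and 6 months post-discharge". For the MoCA it says: "Cognitive impairment will be assessed by the study team before ICU discharge and 6 months post-discharge using the Montreal Cognitive Assessment". No MoCA before allocation is planned. Participant timeline {13} states: "Participant recruitment, enrolment, and allocation will all be targeted for the first 24 h following admission to the ICU". The intervention description {11a} has VR given three times a day until ICU discharge or a maximum of 14 days.

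On missing data, {20c} says: "If missing values occur within the dataset, we will use multiple imputation assuming missing data to be missing at random". It names no exception. Survival at six months is a separate outcome compared between groups ({12}), obtained from a central database ({18a}).

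**The concern.** Two things could distort the answer on long-term outcome.

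First, the word changes, applied to paired time points, leads naturally to a change score. For EQ-5D, FIM and frailty the earlier value describes the patient before ICU admission, so change is measured from a pre-treatment state. For cognition the earlier value is itself a result of treatment. The protocol links delirium to cognitive impairment and expects VR to reduce delirium, so an effect already present at ICU discharge is plausible on its own rationale. Subtracting that effect works against the trial's hypothesis.

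Second, a score after death does not exist; it is not an unobserved value. Missing-at-random imputation would fill it with a prediction learned from survivors, as if the patient had lived. Deaths before six months are foreseeable from the protocol itself: it describes delirium as associated with higher mortality, calls its duration an independent predictor of mortality at 6 and 12 months, and makes six-month survival an outcome. If VR affects survival, the share of invented scores differs between arms.

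**Working it through.** The protocol states no figure for the six-month scores, so there is none to reproduce. The only planned number used here is the arm size of 460 from Sample size {14}. It reproduces: 39% versus 30%, two-sided 0.05 and 80% power with continuity correction gives 459 per arm.

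**Order of events for cognition**

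1. Allocation is targeted within 24 h of ICU admission ({13}).
2. VR runs daily to ICU discharge or at most 14 days ({11a}).
3. The first MoCA is taken before ICU discharge ({12}, {18a}).
4. The second MoCA is taken at six months.

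The first MoCA therefore normally follows both randomisation and exposure. It is a post-treatment measurement.

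**What a change contrast estimates**

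Let d0 be the effect of VR on MoCA at discharge and d6 its effect at six months (assumed values, for illustration).

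- Between-arm difference in change = d6 − d0.
- Between-arm difference at six months adjusted for the discharge score with slope b = d6 − b × d0.

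| Assumed effects | Effect at six months | Change contrast | Adjusted for discharge MoCA, b = 0.5 |
|---|---|---|---|
| d0 = 2, d6 = 2 points | 2 | 2 − 2 = 0 | 2 − 1 = 1 |
| d0 = 0.2, d6 = 0.2 SD | 0.2 | 0.0 | 0.2 − 0.1 = 0.1 |
| d0 = 0.2, d6 = 0.1 SD | 0.1 | −0.1 | 0.1 − 0.1 = 0.0 |
| d0 = 0, d6 = 0.2 SD | 0.2 | 0.2 | 0.2 |

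The change contrast recovers the six-month effect only if VR has done nothing to cognition by discharge. Using the discharge score as a covariate reduces the loss but does not remove it.

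**Reach of the imputation rule**

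Six-month mortality is not given. Assuming 10% to 30%:

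- 460 × 0.10 = 46 per arm (92 of 920)
- 460 × 0.20 = 92 per arm (184 of 920)
- 460 × 0.30 = 138 per arm (276 of 920)

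Under the rule as literally worded, these patients would receive six-month scores. A patient who dies in the ICU would also have no discharge MoCA, and the same question arises there.

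**What the pre-ICU scores could add**

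With the variance of the between-arm difference in the six-month score alone set to 1, a change score has variance 2(1 − r) and a covariate-adjusted comparison 1 − r², where r is the correlation between the two assessments. At an assumed r of 0.3 these are 1.40 and 0.91; at 0.5, 1.00 and 0.75; at 0.7, 0.60 and 0.51. Adjustment is never less precise than the change score. Pre-ICU scores are recalled, sometimes by relatives, so r is unknown and these values only show direction.

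**The case against.** The strongest reply is that the section already intends the right comparison. A reader who stops at the sentence pairing the time points might infer an uncontrolled before-and-after analysis. The text does not support that: the same section goes on to compare the treatment group with the controls, and the third of the further objectives is explicitly between groups. That reply stands in full.

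Next, no section calls the discharge MoCA a baseline. It is listed as an outcome at two times, and if each were compared between arms a lasting benefit would be seen at both. This stands in part. It makes the fault an ambiguity rather than a fixed error, but a comparison of changes between arms is the natural reading of the stated purpose, and for cognition that is change from discharge.

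On death, the protocol never says that scores of deceased patients will be imputed, and an analysis plan not shown here could narrow the rule. A reader might infer that scoring the dead is planned; the text shows only that nothing in it prevents this. But the rule is one the article does state, and it states it without limit.

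Finally, one might call the missing covariate adjustment an error. It is not: the article fixes no model for these scores, that detail commonly sits in an analysis plan, and nothing rules adjustment out. It is a suggestion for precision.

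**Conclusion.** The point holds in two limited parts. The between-arm comparison of the long-term scores is intended but worded as change, and for cognition the earlier score follows randomisation and exposure. A between-arm difference in change would then estimate d6 − d0, which can hide a lasting benefit or reverse the sign of a fading one. Its size depends on the assumed effect at discharge; if that effect is nil, nothing is lost. The imputation rule, as worded, extends to patients who died before six months. The illustration of 46 to 138 per arm rests wholly on an assumed mortality of 10% to 30%.

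It would be wrong to carry this over to the main result. The scores are neither primary nor secondary outcomes, the objective that covers cognition, quality of life and function is to describe differences, and the delirium comparison does not depend on them. Severity is minor.

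**What to change.** - **Cognition:** compare MoCA between arms at ICU discharge and at six months as two separate outcomes, not as change from discharge.
- **EQ-5D, FIM and frailty:** compare the six-month scores between arms, adjusted for the pre-ICU score already collected and for the stratification factors, age and gender.
- **Missing data:** restrict multiple imputation to patients known to be alive at the visit.
- **Death:** report the scores alongside six-month survival and state in advance how death is handled. Whether by a composite, a rank-based analysis or a survivors-only estimand is the sponsor's choice; each answers a different question.

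The cost is a few sentences in {12} and {20c} and the matching code. The scores are already planned, and survival comes from a central database. One item to confirm is whether that source also covers patients classed as drop-outs, for whom {20c} plans no further follow-up.

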**Methods:**

This study is conducted as a randomized clinical trial. A total of 920 critically ill patients in the ICU will participate. The control group will receive standard ICU care, whereas the intervention group will, in addition to the standard ICU care, receive relaxing 360-degree immersive virtual reality content played inside a head-mounted display with noise-cancelling headphones, three times a day. The first 100 patients, regardless of their group, will additionally have their movement patterns recorded using wearable and ambient sensors. Follow-up measurements will take place 6 months after discharge from the ICU.

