### Outcomes {12}

The primary outcome is delirium incidence, measured three times a day (morning, midday, and evening) by the Intensive Care Delirium Screening Checklist (ICDSC) as part of standard assessment. With the ICDSC, delirium is determined by consciousness, inattention, disorientation, hallucination, agitation or retardation, speech and mood, sleep/wake cycle disturbance, and fluctuation [19]. A unique incidence of delirium is counted once a patient reaches a score of ≥ 4, on a scale from 0 to 8 [20]. The entire period that a patient has a score ≥ 4 is considered as a single episode, and accordingly, counts only as a single incidence. The mean incidences of delirium per group will be looked at. The incidence of delirium is considered to be clinically relevant as it is known that patients who experience delirium while in critical care have worse long-term outcomes [4]. Furthermore, due to the possible influence of sedatives and analgesics on the incidence of delirium, both sedation and pain levels will be assessed every 2 h [5]. Consciousness and sedation will be measured using the Glasgow Coma Scale [21] and the Richmond Agitation Sedation Scale [22], respectively, and pain will be measured using the Numeric Rating Scale [23] and the Behavioural Pain Observation Tool [24].

As a secondary outcome, the duration of delirium will be evaluated per 8-h periods, or as needed, while patients are in the ICU. If the participant is assessed as delirious via the ICDSC during any of the assessments during an 8-h span, the entire period will count as delirious. Duration of delirium is clinically relevant knowing that the duration of delirium is an independent predictor of mortality 6 and 12 months post-ICU admission [25, 26].

Additional secondary outcomes include the pattern and intensity of movements, before and during delirium as well as between groups, measured continuously during the ICU stay. The fact that patients in delirium have fluctuating motor performance movement patterns, differing from baseline, could be a possible marker for delirium detection [27]. Therefore, acceleration will be measured with wearable sensors such as inertial measurement units, which have been previously used successfully in the ICU [28]. The monitoring of patients’ movement patterns could provide a means of early detection of delirium, permitting early intervention by the care staff.

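### Survival is counted from ICU discharge with no rule for ICU deaths, the 6-month visit has two anchors, and the imputation rule makes no exception for scores undefined by death

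*Protocol article*

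**What the plan says.** **Survival.** Outcomes {12} places survival among the other pre-specified variables, below delirium incidence (primary) and delirium duration and movement (secondary). The comparison is stated as "Additionally, the average survival 6 months post-ICU discharge will be compared between groups". Plans for assessment {18a} keeps the same origin and names the source: "The average survival 6 months post-discharge will be obtained via a central database". Neither section says how a patient who dies in the ICU is counted.

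**Visit anchor.** The abstract says "Follow-up measurements will take place 6 months after discharge from the ICU", and Participant timeline {13} says "A follow-up visit is planned for 6 months post-ICU discharge". The consent section {26a}, Outcomes {12} and the questionnaire paragraph of {18a} also count from discharge. Later in {18a} the text reads "The study ends with a follow-up assessment 6 months after admission to the ICU".

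**Missing data.** Section {20c} defines the intention-to-treat set as everyone randomised. It closes with "If missing values occur within the dataset, we will use multiple imputation assuming missing data to be missing at random". No exception is made for values that are absent because the participant has died.

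**The concern.** Randomisation is targeted for the first 24 hours after admission, so ICU discharge is a post-randomisation event. Background {6a} links delirium to longer ICU stay and to mortality, and VR is meant to prevent delirium. The starting point of the survival outcome may therefore itself depend on treatment. If only patients discharged alive enter, the compared groups are selected, and an effect on ICU deaths in either direction drops out of sight.

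That matters for safety as well as benefit. Under {22}, adverse events are recorded only if related to VR, so an all-randomised mortality comparison is a useful independent check. Under {17a}, the blinded final analyses are those of delirium incidence and duration. An undefined survival rule could thus be settled by people who know the allocation.

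For the 6-month scores, imputing cognition or quality of life for people who have died creates values that do not exist. It can make an arm with more deaths look equal or better.

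**Working it through.** **1. What the plan lets us compute.** Its only design figure is the 920 total (460 per group) for the primary outcome. With 39% versus 30%, two-sided 0.05 and 80% power, the two-proportion formula with continuity correction gives 459 per arm, 918 in total, so 920 reproduces. It serves below only as a denominator. No ICU mortality, post-discharge mortality or follow-up loss is given, so every mortality rate below is an assumption.

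**2. How many participants the undefined rule touches.** ICU deaths = 920 × assumed ICU mortality:

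- 5%: 920 × 0.05 = 46
- 10%: 920 × 0.10 = 92
- 15%: 920 × 0.15 = 138

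**3. What the two readings show.** Let *m* be ICU mortality and *q* mortality in the 6 months after discharge, with *q* = 10% assumed in both arms.

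- Reading A, discharged alive only: mortality = *q*
- Reading B, ICU deaths counted as deaths: mortality = *m* + (1 − *m*) × *q*

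With equal *m* in both arms, reading A captures 920 × (1 − *m*) × 0.10 deaths:

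| *m* | Captured under A | All deaths (B) |
|---|---|---|
| 5% | 87.4 | 133.4 |
| 10% | 82.8 | 174.8 |
| 15% | 78.2 | 216.2 |

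With unequal *m*:

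| *m* control | *m* VR | A, control vs VR | B, control | B, VR | B difference |
|---|---|---|---|---|---|
| 10% | 7% | 10% vs 10% | 0.10 + 0.90 × 0.10 = 19.0% | 0.07 + 0.93 × 0.10 = 16.3% | −2.7 points |
| 10% | 13% | 10% vs 10% | 19.0% | 0.13 + 0.87 × 0.10 = 21.7% | +2.7 points |

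Reading A shows no difference in either row. Reading B shows the difference. Its remaining defect is that the horizon for those discharged is ICU stay plus 6 months, so observation length differs between participants.

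**4. Fit with the rest of the document.** The all-randomised set in {20c} agrees with B, while the discharge origin in {12} and {18a} points to A. The article's own rationale in {12} uses a third origin: "duration of delirium is an independent predictor of mortality 6 and 12 months post-ICU admission".

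**5. Anchor.** The two statements of the visit date differ by the whole ICU stay. Eligibility requires an expected stay above 24 hours, and in-ICU study assessments stop at 14 days. At 14 days the gap is 14 / 180 ≈ 8% of the follow-up interval; longer stays widen it.

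**6. Imputation.** Suppose a fraction *d* of an arm has died and the dead receive scores predicted from survivors. The arm mean is (1 − *d*) × survivor mean + *d* × predicted mean. The predicted mean describes people as if alive, so a larger *d* carries no penalty for death. The rule's wording reaches these scores. It does not reach vital status, which comes from the central database.

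**The case against.** A reader might infer that the plan excludes ICU deaths. It does not say so. The intention-to-treat set is all randomised patients, vital status comes from a database, and an ICU death could simply be counted as not surviving. This objection stands: the defect is an undefined rule and an awkward origin, not a stated exclusion.

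A reader might also infer that deaths would be imputed as missing at random. No section says this, and the database source speaks against it. The imputation sentence closes a paragraph mainly about superiority testing and drop-outs, and handling of scores truncated by death is often left to the analysis plan. That carries some weight. Still, the sentence states a rule for the whole dataset without qualification, and followed literally it yields scores for the dead.

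Third, importance. Survival is not named in Objectives {7}, and the follow-up scores serve an objective worded as describing differences. Calling mortality the main hard outcome of this trial would go beyond the text.

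Fourth, the single admission-based sentence may be a drafting slip, since the same section elsewhere counts from discharge. That is plausible, but the contradiction still has to be resolved.

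**Conclusion.** The point holds in this limited form. The survival origin is a post-randomisation event that shifts with length of stay, ICU deaths have no stated rule, and the natural reading does not match the all-randomised set. The visit anchor is contradictory. The imputation rule, as written, covers the 6-month MoCA, EQ-5D, functional independence and frailty scores of participants who died.

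The size cannot be derived from the documents. The 46 to 138 participants rest on an assumed ICU mortality of 5% to 15%. The hidden difference of 2.7 points rests on the further assumptions of 10% post-discharge mortality in both arms, a 3-point difference in ICU mortality, and reading A. The primary delirium result is unaffected. This should be changed, but it does not threaten the trial's main conclusion.

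**What to change.** 1. Define survival as death from any cause from randomisation to a fixed time, for example 180 days, in all randomised participants whose data may be used. Count ICU deaths as deaths and take vital status from the central database.
2. Reconcile the 6-month visit anchor across the abstract, {26a}, {12}, {13} and {18a}, so that one anchor is used throughout.
3. Limit imputation under missing at random for the 6-month scores to participants known to be alive. State in advance how death is handled, for example a survivor analysis reported alongside mortality, or a composite that ranks death worst.

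The cost is small but not only wording. Section {20c} ends follow-up for drop-outs, and {18b} anonymises the data of participants who discontinue, which may prevent a later database link. The plan needs a stated provision for their vital status, within their consent, or must say that they are censored.
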